| Day -60 to 0: Subject screening, recruitment, randomization                                 |                                          |
| Sequence A                                                                                  | Sequence B                               |
| 490 m, ZH 1-2                                                                               | 490 m, ZH 1-2                            |
| Oxygen: altitude location at 1650-3000 m                                                    | Sham: altitude location at 1650-3000 m   |
| Wash-out phase                                                                              | Wash-out phase                           |
| Sham: altitude location at 1650-3000 m                                                      | Oxygen: altitude location at 1650-3000 m |

[figure not shown]

**Figure 3:** Baseline examinations will be performed during 2 days at ZH1, ZH2 at 490m. Randomized trial of nocturnal oxygen during two 3-day periods at altitude (1st period: CL1(Samedan 1): day 4 at 1721m; JH1, JH2 (Corvatsch Murtèl 1-2): day 5 and 6 at 2702m; 2nd period CL2 (Samedan 2): day 7 at 1721m; JH3, JH4 (Corvatsch Murtèl 3-4): day 8 and 9 at 2590 m). Patients randomized to sequence A will receive nocturnal oxygen during the 3 days at altitude. After a 2-weeks wash-out period at <800 m, they will spend the 2nd 3-day period at altitude receiving sham oxygen. The sequence of oxygen/sham is reversed in patients randomized to sequence B. The study will end after the 2nd altitude sojourn. If only one altitude location is used, the intermediate day in each study phase (CL1 and CL2) falls away. The studies at JH1 and JH2 will be performed at a moderate altitude of 1650-3000 m, depending on feasibility and logistics.

| Number of examination day                                 | 1     | 2   | 3   | 4   | 5   | 6   | 7   | 8   | 9   |
|-----------------------------------------------------------|-------|-----|-----|-----|-----|-----|-----|-----|-----|
| Visits*                                                   | Recr. | ZH1 | ZH2 | CL1 | JH1 | JH2 | CL2 | JH3 | JH4 |
| Informed consent                                          |       |     |     |     |     |     |     |     |     |
| In-/exclusion criteria                                    |       |     |     |     |     |     |     |     |     |
| Demographic data, past medical history                    |       |     |     |     |     |     |     |     |     |
| Lung function test, aBGA**, 24h ambulatory pulse oximetry |       |     |     |     |     |     |     |     |     |
| Medical history, clinical examination, questionnaires     |       |     |     |     |     |     |     |     |     |
| Polysomnography                                           |       |     |     |     |     |     |     |     |     |
| Reaction tests                                            |       |     |     |     |     |     |     |     |     |
| Echocardiography                                          |       |     |     |     |     |     |     |     |     |
| 6 min walk test                                           |       |     |     |     |     |     |     |     |     |
| Lung function test                                        |       |     |     |     |     |     |     |     |     |
| NIRS*** und Transcranial Doppler                          |       |     |     |     |     |     |     |     |     |
| Spiroergometry                                            |       |     |     |     |     |     |     |     |     |

\*Recr. = Recruitment day. ZH1, ZH2 = Zurich, 490m; CL1, CL2 = Samedan, 1721m; JH1, JH2=, Corvatsch Murtèl 2702 m, 2 and 3 denotes day 2 and day 3 at corresponding altitude. \*\*aBGA= arterial blood gas analysis. \*\*\*NIRS = near infra-red spectroscopy.

**Figure 4:** Overview of all examinations at each location in study phase 2. If only one altitude location is used, the studies CL1 and CL2 fall away, and studies at JH1-JH2 and JH3-JH4 will be performed at a moderate altitude of 1650-3000 m.

### Withdrawal criteria

The following criteria will be considered as indication for withdrawing a patient from the study if treatment with supplemental oxygen or appropriate medical treatment is not readily improving the condition: significant acute mountain sickness (AMS-c score >2); dyspnea at rest; chest pain at rest; systolic blood pressure >200 mmHg, diastolic blood pressure >110 mmHg; SpO2 <80% at rest or <75% during exercise.

### Unblinding criteria

Investigators will be unblinded only after analyses of all data. Exceptions are serious adverse events or other conditions that require immediate knowledge on oxygen or sham treatment to allow prevention of adverse health effects to the patient.

### **4.3 INTERVENTIONS TO MINIMISE BIAS**

The study is designed according to a randomized cross-over trial balanced for the ascent protocol during study phase 1 and to the order of the oxygen and placebo during study phase 2.

Randomization will be performed by letting patients draw an envelope from a set containing a code defining the order of interventions. Envelops will be prepared in a way that assures a balanced design in regard to oxygen/sham and pulsed/continuous oxygen/sham. All patients and investigators are blinded for oxygen/sham or vice versa during study phase 2 by the use of identically looking concentrators producing room air and oxygen.

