**Summary:**

**In study phase 1**, 50 patients with moderate to severe COPD living below 800 m, will be recruited to participate in a randomized cross-over field trial evaluating the hypothesis that exercise capacity during a 4 day sojourn at moderate altitude is reduced in comparison to low altitude. Outcomes will be assessed during 2 days in Zurich (490 m, low altitude baseline), 2 days at Davos Clavadel (1650 m), and 2 days at Davos Jakobshorn (2590 m). The order of altitude exposure will be randomized. The main outcome is the 6 minute walk distance. Additional outcomes are symptom scales, variables from pulmonary function, sleep and vigilance studies, and measures of cardiovascular function. In additional studies 40 patients with precapillary pulmonary hypertension (PH), and 40 patients with interstitial lung disease (ILD) will undergo assessments during 2 days at 490 m, 1 day at 1721 m, and 2 days at 2702 m to evaluate the hypothesis that the 6 minute walk distance is reduced at moderate altitude. If the study locations will not be accessible or will not be appropriate for our needs, the study will take place at different location of comparable altitude. Alternatively, depending on feasibility and logistics, studies will be performed during 2 days in Zurich and during 2 days at only one altitude location, situated between 1650-300 m.

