| Day -60 to 0: Subject screening, recruitment, randomization         |                |                |                |
| Sequence A                                                          | Sequence B     | Sequence C     | Sequence D     |
| 490 m, ZH 1-2                                                       | 490 m, ZH 1-2  | 1650m, CL 1-2  | 2590 m, JH 1-2 |
| 1650 m, CL 1-2                                                      | 2590 m, JH 1-2 | 2590 m, JH 1-2 | 1650 m, CL 1-2 |
| 2590 m, JH 1-2                                                      | 1650 m, CL 1-2 | 490 m, ZH 1-2  | 490 m, ZH 1-2  |

| Table 2a. Randomized sequences of altitude exposure in study phase 1 (PH and ILD patients) |                    |
|--------------------------------------------------------------------------------------------|--------------------|
| Day -60 to 0: Subject screening, recruitment, randomization                                |                    |
| Sequence A                                                                                 | Sequence B         |
| 490 m, Zurich 1-2                                                                          | 1721 m, Samedan 1  |
| 1721 m, Samedan 1                                                                          | 2702 m, Murtèl 1-2 |
| 2702 m, Murtèl 1-2                                                                         | 490 m, Zurich 1-2  |

| Table 2b. Randomized sequences of altitude exposure in study phase 1 (PH and ILD patients) if only one altitude location is used |                                        |
|----------------------------------------------------------------------------------------------------------------------------------|----------------------------------------|
| Day -60 to 0: Subject screening, recruitment, randomization                                                                      |                                        |
| Sequence A                                                                                                                       | Sequence B                             |
| 490 m, Zurich 1-2                                                                                                                | Altitude location (at 1650-3000 m) 1-2 |
| Altitude location (at 1650-3000 m) 1-2                                                                                           | 490 m, Zurich 1-2                      |

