| 
* Assessments will be similar at all study locations with the following exceptions:
 Samedan, 1721m: physiologic evaluation will include spirometry, body plethysmography, diffusing capacity, sniff nasal pressure, maximal exercise (spiroergometry)
 Murtèl Corvatsch, 2702 m: as at 1721 m but without body plethysmography and spiroergometry; instead, measurements of cerebrovascular blood flow and muscle oxygen at rest and during submaximal exercise.
 |       |                                                                                                                     |

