### 8.2 SAMPLE SIZE ESTIMATION

Minimally important differences in the primary outcome and the corresponding SD are defined as follows according to previous studies: 6-minute walk distance: difference of 26 m (SD 55m) Regarding secondary outcomes, our recent studies in healthy subjects and in patients with obstructive sleep apnea syndrome revealed the following changes at 2590 m compared to 490 m: a mean decrease in FVC of 6% (SD 7%); an increase in the BORG rating during the 6 min walk of 0.8 (1.6); a decrease in nocturnal oxygen saturation of 5% (2%). Power calculations indicate a required sample size of 45 COPD patients to detect the minimal differences listed above with a power of 80% at  $\alpha$  0.05. Assuming a drop-out rate of 10%, 50 participants will be recruited.

In patients with PH and ILD minimal important differences in the 6 min walk distance of 35-40 m have been reported. In order to detect a difference of 40 m between values at 490 and 2702 m (SD 90m) with alpha 0.05 and power of 0.80 the required sample size is 42. Accounting for drop-outs the aim is to recruit 50 patients per group.

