### **8.3 STATISTICAL ANALYSIS**

Before analysis, data are anonymized by allocating a numerical code to each participant. Completeness, plausibility and distribution of data will be assessed by inspection of numerical results and graphical display. Normality of distribution will be tested by the Shapiro Wilks statistic. Data will be summarized by means (SD) and medians (quartiles) for normal and non-normal distributions. Effects of treatment and altitude will be evaluated according to the principles of cross-over trial analysis described by Senn S. using ANOVA and multiple regression.

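### Table 2a does not balance altitude over period, so the 42 PH or ILD patients of section 8.2 give 80% power only if period is left out; a full period term gives about 69% at 42 and 77% at 50

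*Protocol*

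**What the plan says.** Protocol section 4.3, on minimising bias, describes phase 1 in these words: "The study is designed according to a randomized cross-over trial balanced for the ascent protocol during study phase 1".

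Section 4.2 gives the orders for the PH and ILD cohorts under "Table 2a. Randomized sequences of altitude exposure in study phase 1 (PH and ILD patients"). Sequence A is 490 m, 1721 m, 2702 m. Sequence B is 1721 m, 2702 m, 490 m. Table 2b is an alternative for the case of a single altitude location, with two periods in both orders.

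Section 8.2 sizes these cohorts on a target of 40 m for 2702 m against 490 m, with an SD of 90 m, and concludes: "with alpha 0.05 and power of 0.80 the required sample size is 42". It then sets the recruitment target: "Accounting for drop-outs the aim is to recruit 50 patients per group". The Summary gives a different phase 1 number: "40 patients with precapillary pulmonary hypertension (PH), and 40 patients with interstitial lung disease (ILD) will undergo assessments".

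On analysis, section 8.3 says: "Effects of treatment and altitude will be evaluated according to the principles of cross-over trial analysis", by ANOVA and multiple regression. It does not list the model terms.

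**The concern.** In a cross-over, a treatment contrast is free of period effects without adjustment only when the compared conditions are spread equally over the periods. In Table 2a they are not: 2702 m never comes first and 490 m never comes second. The walk test is a repeated performance measure, and section 5.1 names no walk among the screening tests, so a difference between the first and second period is plausible.

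If period is left out, any such difference enters the contrast that section 8.2 powers, in both the PH and the ILD cohort. If period is fitted, the bias goes but precision is lost, and the sample size in section 8.2 makes no allowance for that.

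**Working it through.** **Inputs.** Difference 40 m, SD 90 m, alpha 0.05, power 0.80, N = 42, recruitment 50 (section 8.2). Sequences from Table 2a. Assumed: two-sided test; 1:1 allocation; the same SD of 90 m for each pairwise difference, so the within-patient variance is s² = 90²/2 = 4050; a walk at 1721 m. On the last, the footnote to Table 3 says "Assessments will be similar at all study locations with the following exceptions", and the walk is not among the exceptions.

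**1. Reproducing 42.** Paired normal approximation: (90 × (1.96 + 0.84)/40)² ≈ 39.7, so 40. With the noncentral t, 42 is the smallest N reaching 80% (power 80.3%). A one-sided paired test would need 32, and a two-sample comparison 80 per arm. So 42 is the plain two-sided paired figure, with 90 m as the SD of the within-patient difference.

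**2. Position of each altitude.**

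| Altitude | Period in A | Period in B |
|---|---|---|
| 490 m | 1 | 3 |
| 1721 m | 2 | 1 |
| 2702 m | 3 | 2 |

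**3. Contrast with period left out.** Write p1, p2, p3 for the period effects. The mean of 2702 m minus 490 m is

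effect + [(p3 − p1) + (p2 − p3)]/2 = effect + (p2 − p1)/2.

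The protocol gives no value for p2 − p1. As an illustration only, gains of 10, 20 or 30 m from period 1 to period 2 would shift the estimate by 5, 10 or 15 m towards no decrement.

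**4. Contrast with three-level period fitted.** Form c = (2y3 − y1 − y2)/3 for each patient from the three periods. The mean of c in A minus the mean of c in B estimates 2702 m minus 490 m, and all period effects cancel.

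- Variance of c per patient: s²(4 + 1 + 1)/9 = 2s²/3.
- With N/2 patients per sequence: 2 × (2s²/3)/(N/2) = 8s²/(3N).
- Unadjusted paired variance: 2s²/N. The ratio is 4/3.
- At N = 42: SE = √(8 × 4050/(3 × 42)) = 16.04 m, against 90/√42 = 13.89 m.

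Power for 40 m (noncentral t, 2N − 4 df when period is fitted):

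| Evaluable N | Period left out | Three-level period |
|---|---|---|
| 40 | 78.3% | 67.1% |
| 42 | 80.3% | 69.3% |
| 45 | 83.0% | 72.3% |
| 50 | 86.9% | 76.9% |
| 54 | 89.4% | 80.0% |

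At 42, other approximations give 68.2% (N − 2 df), 70.3% (normal) and 67.9% (simulation). A random patient effect gives the same SE.

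**5. Simpler period terms.** A first-period indicator inflates the variance by 1.25: power 72% at 42 and 79% at 50. A linear trend inflates it by 1.083: 78% at 42 and 85% at 50.

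**The case against.** The strongest reply is that the protocol nowhere says period will be ignored. Section 8.3 commits to cross-over principles, and the exact terms belong in a SAP that is not shown. That stands: a reader might infer that the planned analysis is biased, and the document does not support this. But the reply moves the problem to section 8.2, because the usual cross-over model includes period and the 80% at 42 does not allow for it.

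A reader might also infer that these cohorts simply have 69% power. That is too flat. It applies to 42 evaluable patients and a three-level period term; recruitment aims at 50, and simpler terms cost less. It also needs the 1721 m walk, which Table 3 makes likely but which cannot be confirmed because the shading of Figure 2a is lost. Without that walk, a three-level period effect cannot be separated from the 490 m against 2702 m contrast at all.

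It would go too far to say that the altitude decrement will be understated by a given number of metres. No period effect is stated; if periods 1 and 2 do not differ, there is no bias.

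The word balanced can be read as half the patients starting low and half starting at altitude. Table 2a does that, but it does not make altitude balanced over the three periods.

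Finally, the point does not carry over to the COPD sample size. The four sequences of Table 2 inflate the variance by 1.25, yet 45 patients for 26 m (SD 55 m) still give 80.1%.

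**Conclusion.** The point holds for PH and ILD phase 1 under Table 2a. Altitude is not balanced over period there. The unadjusted contrast carries (p2 − p1)/2, of unknown size. The 42 in section 8.2 delivers 80% only when period is left out. With three-level period fitted, power is about 69% at 42, 72% at 45 and 77% at 50 evaluable patients, and 80% needs about 54. The Summary's 40 per group would give about 67%.

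These figures rest on 1:1 sequences, equal SDs of 90 m and use of the 1721 m walk. The two-period option in Table 2b is balanced and keeps about 80% at 42 under the same 40 m and 90 m. This is a moderate point about the stated power and the description of the design; it does not show that the design is unusable.

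**What to change.** 1. In section 8.3, state that the PH and ILD phase 1 model under Table 2a includes patient, altitude and period, and uses the 1721 m walk.
2. In section 8.2, restate power as about 69-77% for 42-50 evaluable patients. Say that 80% at 42 applies only to an unadjusted contrast or to Table 2b.
3. In section 4.3, qualify the word balanced: under Table 2a, order is split between starting low and starting at altitude, but altitude is not balanced over periods.
4. Optionally, name the second-day walks at 490 m and 2702 m as the analysed values; Table 3 schedules a walk on two days. This lessens a first-walk practice effect in the plain contrast but does not replace the period term. The 1721 m stay is one day, so its walk in sequence B would still be a patient's first. By the estimator in step 4 of the working, a first-walk deficit L there would shift the adjusted contrast by L/3 towards a larger decrement. The choice of walk and the model should therefore be fixed together.

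The cost is wording in three sections and a less favourable stated power. Sample size, visits and ascent order stay as they are.

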## **5 PARTICIPANT ENTRY**

### **5.1 RECRUITMENT**

Patients diagnosed with stable COPD, PH or ILD will be asked to participate. They will be recruited among patients attending the Pulmonary Division University Hospital of Zurich and by advertisements distributed to the Zurich Lung League “Lunge Zürich” and newspapers.

During pre-study screening (recruitment examination), a detailed medical history and review of medical records will be performed to identify any risk factors that may predispose to adverse altitude effects (see exclusion criteria). Pulmonary function, arterial blood gases, resting ECG and a 24 h ambulatory pulse oximetry at the patient’s home will be obtained.

### **5.2 INCLUSION CRITERIA**

- COPD diagnosed according to GOLD criteria, grades 2-3.
- Precapillary PH, diagnosed according to international guidelines, NYHA class 2-3.
- Interstitial lung disease diagnosed according to international guidelines, NYHA class 2-3.
- Age 18 to 75 years, both genders.
- Residence at low altitude (<800m).
- Informed consent.

### **5.3 EXCLUSION CRITERIA**

- Unstable condition and COPD exacerbation defined as a change in the dyspnea, cough or sputum production beyond normal day-to-day variation, acute in onset and which may require a change in treatment; a change in baseline medication within the last 30 days.
- Very severe COPD (i.e. GOLD 4, FEV1<30% predicted), severe gas exchange or hemodynamic impairment: diffusing capacity <30% predicted; hypoxemia requiring oxygen therapy at sea level ( $\text{PaO}_2 < 7.3 \text{ kPa}$ ); hypoventilation ( $\text{PaCO}_2 > 6.7 \text{ kPa}$ ); mean pulmonary artery pressure measured by right heart catheter >40 mmHg or pulmonary artery systolic pressure estimated by echocardiography >50 mmHg.
- Patients with very severe PH, NYHA class 4, unstable PH defined by a change of specific drug therapy within the last 30 days, hypoxemia requiring oxygen therapy at sea level ( $\text{PaO}_2 < 7.3 \text{ kPa}$ ); at 490m.
- Patients with very advanced ILD, NYHA class 4, unstable or exacerbated ILD, hypoxemia requiring oxygen therapy at sea level ( $\text{PaO}_2 < 7.3 \text{ kPa}$ ).

- More than mild or inadequately controlled cardiovascular disease such as uncontrolled systemic arterial hypertension, coronary artery disease, previous stroke; obstructive sleep apnea syndrome (overlap syndrome); pneumothorax in the last 2 months.
- Use of drugs that affect respiratory center drive (sedatives or sleep inducing drugs, morphine or codeine derivatives).
- Internal, neurologic or psychiatric disease that interfere with protocol compliance including current heavy smoking (>20 cigarettes per day), inability to perform bicycle exercise.
- Previous intolerance to moderate altitude (<2600m).
- Exposure to altitudes >1500m for >2 days within the last 4 weeks before the study. Pregnant patients (women potentially capable of childbearing, i.e., who are not yet menopausal and had their last menstrual period less than 12 months ago, who had no hysterectomy, ovariectomy, or surgery to occlude the fallopian tubes, will be tested for pregnancy, on site, at the beginning of the study, by urinary  $\beta$ -HCG-concentration (lifeSign Status hCG Serum/Urine). The urine sample will not be stored.)
- Nursing patients.

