| Main Exclusion Criteria: | 
 
- Unstable condition, COPD exacerbation (change in dyspnea, cough or sputum production which may require a change in treatment). Unstable PH (recent requirement for change in treatment), unstable ILD or exacerbated ILD.
 
- Very severe COPD (FEV1 or diffusing capacity <30% predicted, PaO2 at 490 m <7.3 kPa, PaCO2 at 490 m >6.7 kPa)
 
- Very severe PH, very severe ILD (NYHA 4, diffusing capacity <30% predicted, PaO2 at 490 m <7.3 kPa)
 
- More than mild or poorly controlled cardiovascular disease
 
- Use of drugs that affect respiratory center drive.
 
- Internal, neurologic or psychiatric disease that interfere with protocol compliance including current heavy smoking (>20 cigarettes per day), inability to perform bicycle exercise.
 
- Previous intolerance to moderate altitude (<2600m)
 
- Pregnancy
 
 |
| Study Schedule:          | 05/2013 through 12/2016                                                                                                                                                                                                                                                                                                                                                                                                                                                                                                                                                                                                                                                                                                                                                                                                                                                                                                                                                                            |

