#### **Pulmonary hypertension**

Precapillary pulmonary hypertension (PH) has been defined by the WHO as a mean pulmonary artery pressure  $\geq 25$ mmHg along with a pulmonary capillary occlusion pressure  $\leq 15$ mmHg (to differentiate from pulmonary venous hypertension due to left heart disease). PH is either idiopathic or associated with many different disorders such as collagen vascular disease, portal hypertension, hypoxemic lung diseases, chronic thromboembolism, and many more. The leading symptom in PH is dyspnea on exertion with impaired exercise performance. It can be attributed to: 1st) impaired pulmonary gas exchange due to ventilation-perfusion mismatch, and diffusion impairment due to loss of gas exchange surface, 2nd) inadequate increase in cardiac output during exercise leading to lactic acidosis with increased CO2 production thereby increasing ventilatory requirements; and 3rd) exercise induced hypoxemia that worsens PH by

hypoxic pulmonary vasoconstriction. With progression of PH, dyspnea occurs on minimal exertion, and syncope and right heart failure may develop. Although PH is still incurable, recent therapeutic advances, i.e., pulmonary vasodilators and endarterectomy have improved the life expectancy, physical performance and quality of life of PH patients.

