## **11 ETHICAL CONSIDERATIONS**

### **11.1 RISK BENEFIT ASSESSMENT**

Millions of patients with COPD and other chronic lung diseases worldwide travel to moderate altitude for professional or recreational activities. In Switzerland and in other countries COPD patients are even referred for medical treatment in high altitude clinics such as the Hochgebirgsklinik Davos Wolfgang, the Zürcher Höhenklinik Davos Clavadel or the Luzerner and Berner Höhenkliniken in Montana. We expect that our inclusion and exclusion criteria will prevent that the study participants experience clinically relevant harm from the exposure to moderate altitude up to 2702 m. Precautions are taken to have all necessary measures to treat and evacuate patients if necessary.

The benefit of our study is to gain knowledge on health effects of altitude exposure in COPD, PH and ILD patients. This will help to counsel such patients planning altitude travel and to prevent altitude related illness in the future, which is of great value and outweighs the potential risks of the current study by far.

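### The synopsis excludes PH and ILD patients with diffusing capacity below 30% predicted, but the PH and ILD bullets of section 5.3 leave this limit out

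*Protocol*

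**What the plan says.** The synopsis, under main exclusion criteria, treats PH and ILD in one line: "Very severe PH, very severe ILD (NYHA 4, diffusing capacity" below 30% predicted, and PaO2 at 490 m below 7.3 kPa.

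Section 5.3 gives each disease its own bullet.

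- The PH bullet lists "Patients with very severe PH, NYHA class 4, unstable PH defined by a change of specific drug therapy within the last 30 days", followed by hypoxaemia with PaO2 below 7.3 kPa.
- The ILD bullet lists "Patients with very advanced ILD, NYHA class 4, unstable or exacerbated ILD, hypoxemia requiring oxygen therapy at sea level", again with PaO2 below 7.3 kPa.
- The bullet that opens with very severe COPD goes on to "severe gas exchange or hemodynamic impairment: diffusing capacity <30% predicted". It then gives PaO2 below 7.3 kPa, PaCO2 above 6.7 kPa, and "mean pulmonary artery pressure measured by right heart catheter >40 mmHg or pulmonary artery systolic pressure estimated by echocardiography >50 mmHg".

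Section 5.2 requires NYHA class 2-3 for PH and ILD and sets no floor for diffusing capacity.

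Section 11.1, which covers heights as great as 2702 m, states this expectation: "our inclusion and exclusion criteria will prevent that the study participants experience clinically relevant harm from the exposure to moderate altitude".

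**The concern.** Two current lists in the same protocol give different eligibility limits for PH and ILD. The sponsor chose a diffusing-capacity limit for these groups in the synopsis, but the detailed section does not carry it into their bullets. Staff who screen from 5.3 could accept a patient whom the synopsis rules out.

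The matter is one of safety. PH and ILD patients are to spend two days at 2702 m, and the risk-benefit argument of section 11.1 rests on the criteria. The protocol treats impaired gas exchange as relevant to both groups. Section 3.1 names "diffusion impairment due to loss of gas exchange surface" among the causes of exertional dyspnoea and reduced exercise performance in PH, and gas-exchange limitation among the reasons why ILD patients may perform worse at altitude.

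**Working it through.** No arithmetic applies. The check sets the two lists side by side.

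| Limit | Synopsis, PH and ILD | 5.3, PH bullet | 5.3, ILD bullet | 5.3, COPD bullet |
|---|---|---|---|---|
| NYHA class 4 | yes | yes | yes | no |
| PaO2 <7.3 kPa | yes | yes | yes | yes |
| Diffusing capacity <30% predicted | yes | **no** | **no** | yes |
| PaCO2 >6.7 kPa | no | no | no | yes |
| Mean pulmonary artery pressure >40 mmHg, or systolic by echocardiography >50 mmHg | no | no | no | yes |

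**Step 1: are the synopsis limits alternatives?** They are best read so. Section 5.3 makes NYHA class 4 and hypoxaemia separate grounds for exclusion. If all three had to be met together, the line would exclude nobody whom section 5.2 does not already rule out by requiring NYHA class 2-3.

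**Step 2: a test case.** Take a stable PH or ILD patient in NYHA class 3, with diffusing capacity 25% predicted and PaO2 8.0 kPa at 490 m, who meets all other criteria.

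- Synopsis: excluded, because 25% is below 30%.
- Section 5.2: eligible, because class 3 lies within 2-3.
- Section 5.3, PH or ILD bullet: NYHA class 4 is not met, instability is not met, and 8.0 kPa is above 7.3 kPa. No numerical limit excludes the patient.

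**Step 3: does the COPD bullet of 5.3 close the gap?** Its wording on gas exchange and haemodynamics is not expressly confined to COPD. Two features nevertheless favour a COPD-only reading.

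- The synopsis gives the matching diffusing-capacity, PaO2 and PaCO2 limits as the description of very severe COPD. It then states diffusing capacity again for PH and ILD.
- The same bullet carries the pulmonary pressure limits. Section 3.1 begins "Precapillary pulmonary hypertension (PH) has been defined by the WHO as a mean pulmonary artery pressure" of at least 25 mmHg. A general reading would confine the PH group to mean pressures of 25-40 mmHg, which neither the synopsis nor the PH bullet says.

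The repetition of the PaO2 limit in the PH and ILD bullets points the same way, but weakly, because this list repeats itself elsewhere.

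**The case against.** **The lists can be read together.** The PH bullet names very severe PH as an item apart from NYHA class 4, and the synopsis explains that term with a parenthesis that includes diffusing capacity. A screener who applies both lists would exclude the patient, and no text permits an exception. This stands as a limit on the point: the gap opens only when 5.3 is used alone. It does not remove the point. Section 5.3 does not define the term, and its ILD bullet speaks of very advanced rather than very severe disease, so the link to the synopsis is weaker there.

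**Other safeguards remain.** The PaO2, NYHA and instability rules still apply. Screening under section 5.1 looks for risk factors for adverse altitude effects and includes blood gases and 24-hour oximetry. Under section 4.2, SpO2 below 80% at rest or below 75% during exercise is an indication for withdrawal if treatment does not readily improve it. Section 9.1 provides a doctor, oxygen and an evacuation plan. All of this stands, and it means that a patient admitted through the gap is not unprotected. The safeguards are partial, however. The synopsis lists the diffusing-capacity limit beside the PaO2 limit rather than in place of it, and withdrawal comes only after exposure.

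**A reader might infer damage to the analysis**, because sections 8.5 and 8.6 call for a per-protocol analysis of phase 1. The protocol does not support that. Neither section says that patients who breach an eligibility criterion are removed, and phase 2 is analysed by intention to treat.

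**A reader might also infer that the whole COPD bullet should be labelled COPD only.** That goes too far. If the sponsor meant its PaCO2 or pressure limits to be general, the label would remove a safety limit.

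**Conclusion.** The inconsistency is real: one eligibility limit is present in the synopsis for PH and ILD and absent from both of their bullets in 5.3. It deserves correction because it is a safety threshold that the sponsor set for these groups and because section 11.1 relies on the criteria.

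Its size in patients cannot be given. The protocol does not say how many otherwise eligible candidates have diffusing capacity below 30% predicted, nor how pulmonary pressures are distributed in the PH candidates. Any count of patients wrongly admitted, or any share of the PH group lost under a general reading of the pressure limits, would rest on assumption alone. Planned group sizes also vary within the protocol: the synopsis summary gives 40 per disease group for phase 1 and 50 for phase 2, while the synopsis entry on number of subjects and section 8.2 give 50.

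The conclusion rests on two readings: that the synopsis limits are alternatives, and that the COPD bullet of 5.3 is meant for COPD. The first is firm. The second is the more natural reading but not certain, which is why the claim is that 5.3 can admit such patients, not that it must. No sample size, power or other stated figure is affected.

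**What to change.** In section 5.3, add diffusing capacity below 30% predicted to the PH bullet and to the ILD bullet, so that both match the synopsis.

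Separately, ask the sponsor whether the limits in the COPD bullet for pulmonary pressure (mean above 40 mmHg, systolic above 50 mmHg) and for PaCO2 (above 6.7 kPa) apply to COPD only, and state the answer in 5.3. This should not be settled by relabelling the bullet without that confirmation.

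The cost is a short amendment. The protocol is dated 13.12.2013 and Table 1 schedules PH and ILD recruitment from month 4 of 2014, so it can precede enrolment. No new kind of test is needed: section 5.1 includes pulmonary function at screening, and section 6.1 counts diffusing capacity among the pulmonary function tests. The amendment should confirm that it is measured at the screening visit. The small downside is that a few more candidates may fail screening.
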